**Methods:**

This prospective, multicenter, randomized controlled, single-blinded, phase III trial is designed to enroll 512 eligible patients with advanced rectal cancer and preoperative enlarged lateral lymph nodes. The population will be randomly assigned into the solely total mesorectal excision (TME) group or the TME + LLND group after eligible selection. The primary outcomes are to be 3-year local recurrence rate and 3-year disease-free survival, and the secondary outcomes include 3-year overall survival, 1-year sexual and urinary function, and perioperative outcomes.

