## Methods

### Study design

This is a prospective, multicenter, randomized controlled, single-blinded, phase III trial in which patients will be randomly assigned into two parallel comparison groups (the TME + LLND group and the TME group). The flow diagram of this trial is shown in Fig. 1. Our trial began in May 2016 in the West China Hospital of Sichuan University and is expected to end in 2022.

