### Study population

The inclusion and exclusion criteria of our trial are shown in Table 1. All eligible patients will strictly comply with the criteria.

**Table 1 Tab1:** The inclusion and exclusion criteria

Inclusion criteria:
•Age (years): 18–75
•Histologically confirmed rectal cancer
•Clinical stage: cTxN1-2M0 or cT3-4N0M0
•Suspicion of LLN metastasis: short-axis diameter of lateral lymph nodes (LLN) >5 mm; short diameter of common iliac or external iliac lymph nodes >6 mm [16, 24, 25]
•No extramesorectal lymph node swelling (short-axis diameter <10 mm)
•No invasion of other organs
•Performance Status (PS): 0, 1
•No past history of chemotherapy, pelvic surgery, or radiation
•Written informed consent operative criteria:
•Mesorectal excision is performed
•Operative findings:
Main lesion of the tumor is located at the rectum
Lower tumor margin is below the peritoneal reflection
Stage R0 after resection
Exclusion criteria:
•High rectal cancer: lower tumor margin is above the peritoneal reflection
•Multiple-cancer patients
•Pregnant patients
•Patients with psychological disorder
•Steroid administration
•Cardiac infarction within previous 6 months
•Severe pulmonary emphysema and/or pulmonary fibrosis
•Physician’s decision to exclude
•Patients with confirmed LLN metastasis: short-axis diameter of LLN >10 mm and a lymph node with an irregular edge, heterogeneous signal, or obvious enlargement and after nCRT has been completed, lymph node enlarges more than 30%
•Emergency surgery
•Patients with coagulopathies

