### Randomization and blinding

All eligible participants meeting the inclusion criteria will be randomly allocated into either the TME + LLND group or the TME group. Based on one previous study, randomization is performed using a computer-generated, blocked randomization sequence with a block size of 4 at a 1:1 ratio [19]. The patients will be informed about the treatment details upon admission the day before surgery. Owing to the specificity and ethics, this trial allows the participants, the surgeon, and the investigators to be aware of the whole assignment.

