### Data collection and management

We have invited more than 10 large medical centers, which have developed experienced LLND surgery in China, to participate in this trial. We have made universal standards including inclusion and exclusion criteria, nCRT, and TME + LLND standard for all units. In order to obtain good-quality monitoring, we have hired a professional clinical research company to organize and manage the work of all participant units. A Case Report Form is made for each participant to record their data.

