## Discussion

Currently, the hot issue of the treatment of LLN in advanced rectal cancer patients is still being debated in different regions. Eastern countries, especially Japan, favor LLND following TME; however, Western countries believe that nCRT and TME is recommended, and LLDN is added only when a LLN is preoperatively diagnosed as metastatic. Actually, preoperatively enlarged LLNs are not common and only a small proportion of LLDs with a maximum short-axis diameter ≥10 mm, or with a spiculated or indistinct border, or a mottled heterogenic pattern are diagnosed as metastatic [23]. The remaining large proportion of LLNs are underdiagnosed as being metastatic and often confuse surgeons’ treatment strategy. Thus, our trial pays particular attention to this stratification of suspicious LLNs, assessing the efficacy and safety of the LLND in advanced rectal cancer patients.

Another issue we have considered in our trial is the randomization time. In our trial, we randomly allocated participants before nCRT rather than after nCRT. Because LLN metastases are commonly diagnosed before nCRT by their features on pelvic MRI or CT and when chemo-radiation has achieved its effect, the treatment-sensitive regions of any enlarged LLNs will have decreased in size which may confuse the randomization if allocation is performed after nCRT.

This trial is the first randomized controlled trial to investigate the role of LLND in reducing local recurrence rates for low advanced rectal cancer patients with suspicion of LLN metastases. If the efficacy of LLND is verified, which reduces the local recurrence rate from 15% to 8%, LLND can be recommended as a new standard strategy for low advanced rectal cancer patients with suspicion of LLN metastases.

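### The trial is labelled single-blinded, yet participants, surgeon and investigators may all know the arm and no blinded party is named; the fixed block size of 4 is a secondary, conditional weakness

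*Protocol article*

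**What the plan says.** The abstract's Methods paragraph opens "This prospective, multicenter, randomized controlled, single-blinded, phase III trial is designed to enroll 512 eligible patients", and the Study design section repeats the label: "This is a prospective, multicenter, randomized controlled, single-blinded, phase III trial".

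The Randomization and blinding section is the only place that deals with who knows the allocation. It says "this trial allows the participants, the surgeon, and the investigators to be aware of the whole assignment", and on timing it adds "The patients will be informed about the treatment details upon admission the day before surgery". No outcome assessor, radiologist, pathologist or statistician is described as blinded anywhere in the article.

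The same section specifies a "blocked randomization sequence with a block size of 4 at a 1:1 ratio". The Discussion states that "we randomly allocated participants before nCRT rather than after nCRT", and the Data collection and management section says "We have invited more than 10 large medical centers". Table 1 lists the physician's "decision to exclude" among the exclusion criteria, without further conditions.

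Under Outcomes, a growing pelvic mass on CT or MRI is one of three accepted ways to diagnose local recurrence, beside biopsy and PET-CT. Under Follow-up, biopsy or PET-CT is done when needed for the diagnosis.

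**The concern.** A reader takes single-blinded to mean that one identified group is kept unaware of treatment. That is usually the patients or the outcome assessors. Here the patients, the surgeon and the investigators are all allowed to know, and no other group is named. Anyone judging risk of bias from the label would credit the trial with a protection that the text does not describe. What is at stake is ascertainment of a primary endpoint that can rest on an imaging judgement.

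The block size adds a second question. Where staff know past assignments, a single published block size lets them work out some of the next ones, and an open-ended exclusion criterion leaves room to act on a prediction. How far this applies depends on arrangements that the article does not give.

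**Working it through.** **Blinding: the statements side by side**

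| Party | What the article says |
|---|---|
| Participants | may know; told the day before surgery |
| Surgeon | may know |
| Investigators | may know; time of learning not stated |
| Scan readers, pathologist, statistician | not mentioned |
| Whole trial | single-blinded (abstract, Study design) |

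Telling patients late does not rescue the label. DFS and OS are counted from surgery, and the sexual and urinary function scores are wanted at 1 year after it. Patients know their arm before any of these outcomes is assessed.

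**Block size: inputs.** Block of 4, 1:1, from the Randomization and blinding section; more than 10 centres, from Data collection and management. The article gives no predictability figure to reproduce.

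*Case A: a list per centre, every earlier assignment visible, block size known.* There are 6 possible blocks.
- Certain allocations: position 4 always, and position 3 in the 2 of 6 blocks that begin with two alike. (1 + 1/3)/4 = 1/3 = 33.3%.
- Best guess (the arm with more places left), by position: 1/2, 2/3, 2/3, 1. The mean is 17/24 = 70.8%, against 50% by chance.

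*Case B: one list over 10 equally recruiting centres (assumed), each seeing only its own patients and guessing the opposite of its last allocation.*
- The site's last patient lies in the current block with probability 1 − 0.9^(i−1) at position i: 0, 0.1, 0.19, 0.271. The mean is 0.140.
- If so, the guess is right with probability 2/3; otherwise 1/2.
- Success = 1/2 + 0.140 × (2/3 − 1/2) = 52.3%. A simulation of a 512-patient list also gives about 52%.

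*Case C: as A, but assignments become known late.* Best guess by position:
- One patient behind: 1/2, 1/2, 2/3, 2/3; mean 58.3%.
- Two behind: 1/2, 1/2, 1/2, 2/3; mean 54.2%.
- Three behind: 50%.

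*Effect of other block sizes under the full visibility of Case A*

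| Blocks | Certain | Best guess right |
|---|---|---|
| Fixed 4 | 33.3% | 70.8% |
| Fixed 6 | 25.0% | 68.3% |
| Fixed 8 | 20.0% | 66.6% |
| Undisclosed random mix of 4, 6, 8 | mostly removed | about 68% |

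The last figure weights each block size by its length: (4 × 17/24 + 6 × 41/60 + 8 × 373/560)/18 = 12.26/18 = 68.1%. Guessing the under-represented arm needs no knowledge of block size, so varying the size removes certainty far more than it lowers the average guess.

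**The case against.** The strongest reply is that the article names three parties who may know the arm and is silent on scan readers and the statistician, so a blinded reader may exist. That stands as far as it goes. The supportable statement is that the blinded party is not identified, not that there is none. For the same reason, a reader might infer that recurrence will be called by people who know the arm. The article does not say who reads the scans. It also requires the mass to be growing and provides for biopsy or PET-CT when needed.

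A reader might also infer that the fixed block makes the randomisation open to selection bias that no analysis can repair. The text does not carry that.
- The 33.3% and 70.8% need per-centre lists and prompt sight of every earlier assignment. Neither is stated, and the wording describes one sequence with no mention of centre.
- Both arms receive the same chemo-radiation after randomisation, so treatment does not reveal the arm before surgery. If investigators also learn late, predictability drops as in Case C; if they learn at randomisation, it does not.
- How allocation is concealed is a detail that an article commonly leaves to the full protocol.
- Exclusion at the physician's discretion is a common clause, and the article randomises patients who have already met the criteria. The planned Cox models address measured imbalance, though not unmeasured selection.

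What survives is the contradiction over the label, which needs none of these assumptions.

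**Conclusion.** The blinding statements contradict each other and should be reconciled. This is wrong as written and rests on no assumption. Its effect on the local recurrence comparison cannot be quantified from the article, and nothing there shows that bias has occurred.

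The block-size point is secondary. Best-guess success ranges from about 52% (one list, about 10 equal centres, each site seeing only its own patients) to 70.8% with one third of allocations certain (per-centre lists, full and prompt visibility). The article does not place the trial within that range, so the upper figure should not be quoted as the trial's own.

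**What to change.** **Label (main change).** Choose one:
- Keep the radiologists who already read the CT/MRI scans in Table 2 unaware of the arm, and name them as the blinded party in the Randomization and blinding section. This means leaving the arm off the scan requests; no extra readers or scans are needed. Post-operative appearances may sometimes suggest the operation, so masking may be incomplete. It would not cover the patient-reported function scores, which should be described as unblinded.
- Otherwise, replace single-blinded with open-label in the abstract and in Study design. This costs only wording.

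**Block size (secondary).** The article says the trial is still enrolling. For the remaining patients, use randomly varying block sizes, for example 4, 6 and 8, not disclosed to sites. This costs a new computer list, a small protocol amendment and slightly looser running balance. The gain is mainly the loss of certain predictions, since average guessing under full visibility falls only from 70.8% to about 68%. Centre stratification is not required for this purpose; it is a separate design choice, and it would give each site its own sequence to follow.

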### Intervention

After randomization, all participants will firstly receive a cycle of 5-fluorouracil with oxaliplatin therapy (FOLFOX) or capecitabine (Xeloda) with oxaliplatin therapy (XELOX). Subsequently, radiotherapy with 50.4 Gy is administered in 28 separate doses. Next, three cycles of FOLFOX or XELOX will be continued. About 3 to 4 weeks later, patients allocated to the TME group will undergo standard TME surgery solely, while patients allocated to the TME + LLND group will undergo standard TME surgery plus LLND. The extent of LLND includes bilateral LLND (lymph node groups 263P, 263D, and 283). If the short-axis diameter of the external iliac or common iliac lymph nodes is beyond 6 mm, lymph node groups 293, 273, and 280 will be dissected. Unilateral LLND will be done only when the center of the rectal tumor is limited to a single side (not beyond the midline) and the contralateral lymph nodes are not enlarged. Adjuvant chemotherapy, consistent with the preoperative scheme in every patient, will be continued until reaching eight cycles.

### Outcomes

The primary outcomes of this trial are the 3-year local recurrence rate and 3-year disease-free survival (DFS). The local recurrence is defined as recurrent disease in the pelvis or at the incision and DFS is defined as the time of surgery to the recurrence or end of follow-up. It is diagnosed using the following methods: (1) histological confirmation by biopsy, (2) confirmation by positron emission tomography-computed tomography (PET-CT), (3) CT/magnetic resonance imaging (MRI) shows that there is a mass in the pelvis which is growing with/without symptoms.

The secondary outcomes include 3-year overall survival (OS) and disease-free survival (DFS) at 3 years post surgery, sexual and urinary function at 1 year post surgery, and perioperative outcomes. OS is defined as the time of surgery to the date of death from any cause or the date of follow-up. Sexual function for men and women is assessed by using the International Index of Erectile Function-5 scoring system (IIEF-5) and the Female Sexual Function Index (FSFI), respectively [20, 21]. Urinary function is assessed by using the International Prostate Symptom Score (IPSS) [22]. Perioperative outcomes include operation time, intraoperative blood loss, intraoperative transfusion, incision length, intraoperative complications, time to first flatus, time to liquid diet intake, postoperative hospitalization days, postoperative complications, and mortality.

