### Sample size and statistical analysis

Our trial aims to demonstrate that LLND could decrease the 3-year local recurrence rate of low rectal cancer patients with suspicion of LLN metastases. Based on previous studies, we assume that the 3-year local recurrence rate for patients with suspicion of LLN metastases who do not undergo LLND is 15% [13–16], and LLND is expected to show a reduction of 7 percentage points. G*Power 3.1 is used to calculate the sample size. A statistical power of 0.80 and a significance level of 0.05 are chosen, and we assume that there will be a 10% dropout rate. Therefore, 512 patients are needed in this specific trial (256 patients in each group).

All participants in this trial will be analyzed using the intention-to-treat analysis. The chi-square test and Student’ *t* test will be used to compare categorical data and continuous data for the two groups, respectively. The 3-year local recurrence rate, the primary endpoint of this trial, will be analyzed using the Kaplan-Meier method, as well as OS and DFS. In addition, based on different characteristics (such as age, sex, tumor stages, etc.), which can identify the influence of competing risk factors, the Cox proportional hazards (PH) regression model will be tested if Schoenfeld Residuals Analysis confirms PH assumption validation. Otherwise, an alternative extended Cox PH model will be used. SPSS 21.0 (SPSS Inc., Chicago, IL, USA) will be used for all statistical analyses, and a *P* value < 0.05 is considered significant.

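### The protocol gives 3-year DFS two ranks and the trial either one or two primary endpoints, depending on the section, so its criterion for success is not fixed

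*Protocol article*

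**What the plan says.** The protocol article ranks the endpoints in four places.

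- **Abstract, Methods:** two primary outcomes. "The primary outcomes are to be 3-year local recurrence rate and 3-year disease-free survival".
- **Outcomes, first paragraph:** the same two. "The primary outcomes of this trial are the 3-year local recurrence rate and 3-year disease-free survival (DFS").
- **Outcomes, second paragraph:** DFS at the same time point becomes secondary. "The secondary outcomes include 3-year overall survival (OS) and disease-free survival (DFS) at 3 years post surgery".
- **Sample size and statistical analysis:** one primary endpoint, with DFS placed beside OS. "The 3-year local recurrence rate, the primary endpoint of this trial, will be analyzed using the Kaplan-Meier method, as well as OS and DFS".

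The statistics section sizes the trial only on local recurrence: 15% without lateral node dissection, a 7-point reduction, 10% dropout, 512 patients. For the error rates it says "A statistical power of 0.80 and a significance level of 0.05 are chosen". One threshold covers all analyses: a P "value < 0.05 is considered significant". The Discussion gives the only statement of what would change practice, and it concerns local recurrence: "which reduces the local recurrence rate from 15% to 8%, LLND can be recommended as a new standard strategy".

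**The concern.** Which endpoint is primary decides whether a confirmatory trial is positive. Here the same endpoint at the same time point is both primary and secondary within one section, and the count of primary endpoints is two in the Abstract and Outcomes but one in the statistics section.

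Suppose local recurrence misses significance and DFS reaches P < 0.05. The Abstract and Outcomes would then support calling the trial positive on a primary outcome, while the statistics section and Discussion would make it negative. The reading could be chosen once the results are known. The error rate and the power both depend on that choice.

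**Working it through.** **Inputs from the protocol article.** Local recurrence 15% versus 8%, level 0.05, power 0.80, dropout 10%, 256 per arm (Sample size and statistical analysis; Discussion). After 10% loss, 256 × 0.9 = 230 per arm.

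**Inputs that are assumptions.** The article gives no DFS event rate and no correlation between the two tests. I take control DFS event rates of 30% to 50% and correlations of 0 to 0.7.

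**1. The plan's own figure.** For two proportions with pooled variance under the null and no continuity correction,

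n per arm = [z_α √(2p̄(1−p̄)) + z_β √(p1(1−p1) + p2(1−p2))]² / (p1−p2)²,

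with p1 = 0.15, p2 = 0.08, p̄ = 0.115 and z_β = 0.842.

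- One-sided 0.05 (z_α = 1.645): (0.742 + 0.377)² / 0.0049 = 256 per arm, 512 in total, before any dropout.
- Two-sided 0.05 (z_α = 1.960): (0.884 + 0.377)² / 0.0049 = 325 per arm, 650 in total, before any dropout.

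The stated 512 is therefore reproduced only one-sided and without the 10% dropout. Dividing by 0.9 gives 285 per arm (570) one-sided and 362 per arm (724) two-sided. DFS enters none of these.

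**2. Reading A: local recurrence alone is primary.** There is one test at 0.05, so the type I error is 5%.

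**3. Reading B: success on either endpoint counts.** With two tests at 0.05, the upper value is 1 − 0.95² = 0.0975. For correlated test statistics the error is 1 − P(|Z1| < 1.96, |Z2| < 1.96) under a bivariate normal:

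| Correlation | Family-wise error, two-sided |
|---|---|
| 0 | 9.75% |
| 0.3 | 9.5% |
| 0.5 | 9.1% |
| 0.6 | 8.75% |
| 0.7 | 8.3% |

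The Background puts local recurrence at almost 30% of all recurrences. Treating local recurrence as nested within DFS events, the correlation is √[pL(1−pD) / (pD(1−pL))]. With pL = 0.15 and pD = 0.15/0.30 = 0.50 it is √(0.075/0.425) = 0.42; with pL = 0.08 and pD = 0.08/0.30 = 0.267 it is 0.49. The error is then about 9.1% to 9.3%. That 30% describes rectal cancer in general, not patients with enlarged lateral nodes, so it is only a guide.

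**4. Reading C: both must succeed.** The type I error is at most 5%, and power becomes the problem. Suppose the only DFS gain is the 7-point local recurrence gain. Then power = Φ{[|p1−p2| √n − 1.96 √(2p̄(1−p̄))] / √(p1(1−p1) + p2(1−p2))} with n = 230, so |p1−p2| √n = 0.07 × √230 = 1.062.

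| Endpoint | Rates | Argument of Φ | Power, two-sided |
|---|---|---|---|
| DFS events | 50% vs 43% | (1.062 − 1.383)/0.704 = −0.456 | 32% |
| DFS events | 40% vs 33% | (1.062 − 1.334)/0.679 = −0.402 | 34% |
| DFS events | 30% vs 23% | (1.062 − 1.223)/0.622 = −0.260 | 40% |
| Local recurrence | 15% vs 8% | (1.062 − 0.884)/0.448 = 0.395 | 65% |

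The power to succeed on both cannot exceed the DFS figure. Tested one-sided at 0.05, DFS power is about 44% to 52% and local recurrence power about 76%.

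**The case against.** The best defence is that everything tied to a decision points to local recurrence: the stated aim, the sample size, the words the primary endpoint in the statistics section, and the Discussion's condition for recommending the operation. On that view DFS is loosely labelled and the error rate is 5%. This stands as evidence of what was probably meant, and it supports the fix. It does not remove the contradiction, because the Abstract and Outcomes still call DFS primary.

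A second defence is that this is a condensed article and that a testing order or alpha split may be in an analysis plan not shown here. That also stands, so the absence of a multiplicity procedure is not the point. An unseen document cannot, however, make Outcomes agree with itself or with the statistics section.

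A reader might infer that the trial's false-positive rate is about 9%. The document does not support this. That figure needs a rule that either endpoint suffices, and no section states one.

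A reader might also infer that a local recurrence test at two-sided 0.05 would match the planned size. It would not: 256 per arm gives 80% power only one-sided and without dropout. The article does not state the sidedness.

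Finally, the DFS power figures assume no DFS benefit beyond local recurrence. A wider benefit would raise them.

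**Conclusion.** The endpoint hierarchy is wrong as written, and this follows from the text without any assumption. Its numerical effect is conditional:

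- **Local recurrence alone primary:** 5% error, and the Abstract and Outcomes are mislabelled.
- **Either endpoint suffices:** up to 9.75%, and still about 8.3% at a correlation of 0.7.
- **Both required:** error at most 5%, but success is limited by two-sided DFS power of about 32% to 40% under the assumed rates and effect, against about 65% for local recurrence at the same 230 per arm.

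Confidence is high for the contradiction. The sizes depend on which unstated rule is taken and on the assumptions listed. Because it concerns the primary endpoint of a phase III trial, it must be settled before outcome data are examined.

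**What to change.** Make 3-year local recurrence the sole primary endpoint, in line with the endpoint used in the statistics section and the Discussion. Delete DFS from the primary outcomes in the Abstract and in Outcomes. Keep a single DFS entry as the first key secondary endpoint, tested only if local recurrence is significant, followed by OS. Check that the registry record, which was not available here, agrees.

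State separately whether the 0.05 level is one-sided or two-sided. At two-sided 0.05, local recurrence power is about 70% at 256 per arm and 65% at 230, so rewording the endpoints does not settle the sample size.

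The cost is wording in the protocol and analysis plan, and DFS can no longer be claimed as a primary success on its own. Keeping both endpoints as primary would also be coherent if the rule were written down, but it costs more. Splitting alpha to 0.025 each would need 394 per arm two-sided for local recurrence (438 with dropout), or 325 one-sided (362 with dropout), against the 256 planned. Requiring both would carry the DFS power shown above.

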Despite this, existing retrospective cohorts mainly focus on all middle/low advanced rectal cancer patients, not the specific individuals with suspicion of LLN metastases. And those results indicate almost no differences in local recurrence and overall survival, except for longer operation time, more blood loss, and more perioperative complications for LLND [7–9, 18]. A Korean report enrolled 900 advanced rectal cancer patients with preoperative swollen LLNs, which showed that the recurrence rate was associated with the diameter of the LLNs [16]. However, there is no strict prospective randomized controlled study on the comparison of TME + LLND and TME for low rectal cancer with suspicion of LLN metastases after nCRT. Thus, the objective of this study is to assess the efficacy and safety of LLND for low rectal cancer patients with suspicion of LLN metastases (TME + LLND versus TME). Furthermore, the risk factors (such as radiologic factors, pathologic factors, and serum protein) to predict local recurrence and overall survival will be further investigated.

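### The DFS definition names recurrence as its only event, so as written it measures time to recurrence rather than disease-free survival

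*Protocol article*

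**What the plan says.** The Outcomes section of the protocol article names two primary outcomes, the 3-year local recurrence rate and 3-year DFS. Of the second it says: "DFS is defined as the time of surgery to the recurrence or end of follow-up". The next paragraph of that section lists DFS again: "The secondary outcomes include 3-year overall survival (OS) and disease-free survival (DFS) at 3 years post surgery". It then defines overall survival: "OS is defined as the time of surgery to the date of death from any cause or the date of follow-up". Death otherwise appears only at the end of the list of perioperative outcomes: "postoperative hospitalization days, postoperative complications, and mortality".

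Under Sample size and statistical analysis, the 3-year local recurrence rate "will be analyzed using the Kaplan-Meier method, as well as OS and DFS". The same paragraph plans Cox models on patient characteristics "which can identify the influence of competing risk factors".

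**The concern.** An endpoint called disease-free survival should fail when a patient dies, whether or not the cancer has returned. The written definition has only one way to fail, recurrence. A patient who dies without recurrence, including one who dies after the operation, has no event and has reached the end of follow-up. Kaplan-Meier would drop that patient from the risk set as censored and treat the patient as still able to recur later.

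Two things are at stake. First, the 3-year figure reported as DFS would be higher than the proportion of patients alive and free of disease. Second, the trial adds a procedure to a standard operation. If deaths without recurrence differed between the arms, a named primary outcome could not register the difference.

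**Working it through.** **Reading the text**

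1. The DFS and OS sentences have the same form: a start at surgery, an event, then a follow-up date. In the OS sentence the event is death from any cause. In the DFS sentence it is recurrence alone.
2. The end of follow-up in the DFS sentence cannot itself be an event, because it also applies to patients who finish three years in remission. It can only be the censoring side. A recurrence-free patient who dies has nowhere else to fall.
3. Nothing else in the article adds death to DFS. The phrase "which can identify the influence of competing risk factors" refers to characteristics such as age, sex and stage in a Cox model. It does not make death a competing event.

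**Size**

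The article gives no DFS rate, no DFS effect and no rate of death without recurrence, so there is no DFS figure to reproduce. All rates below are assumptions. Let r be the 3-year probability of recurrence and q the 3-year probability of death without recurrence, taken as independent.

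- Endpoint as written: 3-year DFS = 1 − r.
- Endpoint counting death: 3-year DFS = (1 − r)(1 − q).
- Overstatement of the level in an arm: (1 − r) − (1 − r)(1 − q) = (1 − r)q.

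*Level in one arm.* Assume q of 3–8% and 1 − r of 60–90%.

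- Low end: 0.60 × 0.03 = 0.018, or 1.8 points.
- High end: 0.90 × 0.08 = 0.072, or 7.2 points.

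The overstatement is therefore about 2–7 points.

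*Difference between arms.* Assume r = 30% with TME and 25% with TME + LLND. As written, the benefit is 30 − 25 = 5.0 points whatever the death rates. Counting death, the failure rate in each arm is 1 − (1 − r)(1 − q):

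| q, TME / TME + LLND | Failure, TME | Failure, TME + LLND | Benefit |
|---|---|---|---|
| 1% / 1% | 1 − 0.70 × 0.99 = 30.70% | 1 − 0.75 × 0.99 = 25.75% | 4.95 points |
| 5% / 5% | 1 − 0.70 × 0.95 = 33.50% | 1 − 0.75 × 0.95 = 28.75% | 4.75 points |
| 2% / 3% | 1 − 0.70 × 0.98 = 31.40% | 1 − 0.75 × 0.97 = 27.25% | 4.15 points |
| 2% / 5% | 1 − 0.70 × 0.98 = 31.40% | 1 − 0.75 × 0.95 = 28.75% | 2.65 points |

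In the last row, with 256 patients per arm, the deaths not counted as events are 256 × 0.70 × 0.02 = 3.6 and 256 × 0.75 × 0.05 = 9.6, or about 4 versus 10.

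With equal death rates the difference moves by at most 0.25 points. It moves materially only when an excess of deaths with LLND is assumed.

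**The case against.** **Censoring is inferred.** The article never says in words that deaths are censored. It is a condensed account, and censoring rules commonly sit in the full protocol or analysis plan, which are not shown. The label itself is disease-free survival. This limits how firmly one can say what the analysts will do. It does not remove the point, because the definition is stated rather than left out. An analysis plan that followed it would carry the fault forward, and one that counted death would contradict the published definition.

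**Bias in favour of LLND.** A reader might infer that the definition hides fatal harm and so favours LLND. The Background does report "longer operation time, more blood loss, and more perioperative complications for LLND", but the same sentence reports almost no difference in overall survival. That supports more complications, not more deaths. The direction of any bias is therefore conditional on an excess that the article does not show.

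**Deaths lost to the trial.** A reader might also infer that deaths would go unseen. They would not: OS counts death from any cause, and mortality is a perioperative outcome.

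**The 7-point benchmark.** It is tempting to set the overstatement against the planned 7-point effect. That effect is the assumed fall in local recurrence, from 15% to 8%. No DFS effect is stated, so the comparison would mix endpoints.

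**Weight of DFS in the trial.** The sample size section calls local recurrence the primary endpoint, and the aim, the sample size and the success statement in the Discussion rest on it alone. DFS is listed as secondary as well as primary. This stands, and it lowers the severity.

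**Conclusion.** The point holds as a fault in a stated definition. DFS as written omits death, so under Kaplan-Meier it is naturally read as time to recurrence with deaths censored. The reported 3-year level would be too high, by about 2–7 points in an arm if 3–8% die without recurrence and 60–90% are recurrence-free. Those rates are assumptions, since the article gives none.

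The effect on the treatment comparison is small if such deaths are balanced. It becomes material only if they are more frequent with LLND, which the article does not establish. The powered local recurrence comparison is not affected by the DFS definition. The definition should be fixed, but it does not undermine the trial's main result.

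**What to change.** Choose one of the following, in the protocol and in the analysis plan, before outcomes are analysed:

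- **If disease-free survival is intended:** define the event as the first of local recurrence, distant recurrence or death from any cause. Censor only patients who are alive and recurrence-free, at their last disease assessment.
- **If recurrence alone is intended:** rename the endpoint time to recurrence and treat death without recurrence as a competing event.

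The first option costs one sentence. Dates of death are already needed for OS, so no new data are required. The second needs the same data and a competing-risks analysis in place of plain Kaplan-Meier.
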